## Abstract

**Background:**

Almost one in three Australian adults are now obese, and the rate continues to rise. The causes of obesity are multifaceted and include environmental, cultural and lifestyle factors. Emerging evidence suggests there may be temporal patterns in weight gain related, for example, to season and major festivals such as Christmas, potentially due to changes in diet, daily activity patterns or both. The aim of this study is to track the annual rhythm in body weight, 24 h activity patterns, dietary patterns, and wellbeing in a cohort of Australian adults. In addition, through data linkage with a concurrent children’s cohort study, we aim to examine whether changes in children’s body mass index, activity and diet are related to those of their parents.

**Methods:**

A community-based sample of 375 parents aged 18 to 65 years old, residing in or near Adelaide, Australia, and who have access to a Bluetooth-enabled mobile device or a computer and home internet, will be recruited. Across a full year, daily activities (minutes of moderate to vigorous physical activity, light physical activity, sedentary behaviour and sleep) will be measured using wrist-worn accelerometry (Fitbit Charge 3). Body weight will be measured daily using Fitbit wifi scales. Self-reported dietary intake (Dietary Questionnaire for Epidemiological Studies V3.2), and psychological wellbeing (WHOQOL-BREF and DASS-21) will be assessed eight times throughout the 12-month period. Annual patterns in weight will be examined using Lowess curves. Associations between changes in weight and changes in activity and diet compositions will be examined using repeated measures multi-level models. The associations between parent’s and children’s weight, activity and diet will be investigated using multi-level models.

**Discussion:**

Temporal factors, such as day type (weekday or weekend day), cultural celebrations and season, may play a key role in weight gain. The aim is to identify critical opportunities for intervention to assist the prevention of weight gain. Family-based interventions may be an important intervention strategy.

**Trial registration:**

Australia New Zealand Clinical Trials Registry, identifier ACTRN12619001430123. Prospectively registered on 16 October 2019.

## Background

Australian obesity rates are amongst the highest in the world. Almost one in three Australian adults are obese (31%), and a further third are overweight (36%) [1]. Out of the 34 OECD countries, Australia’s adult obesity rate ranks 5th highest, and has shown large increases over the past 10 years, in contrast to counties that are reporting modest growth (Canada and Spain) or even stabilisation (US and UK) [2]. Excess weight, and obesity in particular, is a major risk factor for numerous health conditions including cardiovascular disease, type 2 diabetes, some musculoskeletal conditions and some cancers [3–5]. In 2017, the total annual cost of obesity in Australia was estimated at $11.8 billion [6]. Fully understanding the mechanisms underpinning obesity is crucial if targeted and effective obesity programs are to be developed.

The determinants of obesity are complex. Ecological models recognise they include individual, social, and environmental factors. In particular, excess energy intake through unhealthy eating patterns, insufficient energy expenditure due to lack of physical activity and excess sedentary behaviour, and unhealthy sleep, have been highlighted as key modifiable individual risk factors [7, 8]. Such risk factors are socially and geographically patterned and tend to cluster within individuals and families. In particular, people with lower socioeconomic status are more likely to be overweight or obese, this gap is wider in women, and people in regional areas are more likely to be overweight or obese [9]. Family factors, such as meal-time patterns, parenting style and work patterns have also been show to influence childhood obesity [10]. While we recognise that these determinants have genetic, social and geographical origins, less attention has been paid to temporal patterning.

### Weight gain across the year

Longitudinal studies suggest that, on average, Australian adults aged less than 65 years gain around 0.5 kg [11] and 0.6 cm of waist girth [11, 12] per year. However, the temporal patterning of this weight gain across the year is poorly understood. Research suggests that both weekly and annual cycles in day type (weekday and weekend days), cultural events, and season intertwine to influence adults’ weight gain, activity patterns and eating patterns across the year, as outlined below.

Studies of days of the week suggest health behaviours may differ between weekdays and weekend days. For example, a US study of 9000 adults found that energy intake was 6% higher on weekend days compared to weekdays, with increased proportions of energy from fat and alcohol on weekends [13]. In addition, studies have suggested physical activity is lower on weekend days than weekdays [14, 15], while sleep duration is longer on weekend days [16, 17].

Studies of festive periods, and particularly the “holiday season” (in the West, from around late November through to early January, taking in Thanksgiving, Christmas and New Year’s Eve) show that weight gain coincides with cultural celebrations. US “holiday season” weight gain is consistently 0.4–0.9 kg [18], and it appears that average weight gain over this 6-week period may account for the majority of annual weight gain [19]. A study of weight change in three Northern Hemisphere countries (US, Germany and Japan) found that weight gain coincided with cultural celebrations, however the relative importance of celebrations for weight gain varied between countries – in particular, the percentage weight gain at Christmas and Easter in Germany was almost double that for the US, and in Japan, most weight gain occurred during the May “Golden Week” celebration [20].

Studies of seasonal changes in weight and health behaviour suggest weight peaks in winter and troughs in summer [21]. Seasonal differences in energy and nutrient intake have been reported, though they are generally small in magnitude, and the direction of such differences is inconsistent between studies [13, 22]. Similarly, some studies have shown that adults sleep more in winter [23, 24], while others have shown no seasonal difference in sleep [25, 26]. Adult studies in the US and Europe found that people are relatively more active in summer than in winter [27–29]. However, a recent study of children suggests different patterns may occur in Australia and Canada– while Canadian children were relatively more active in summer than winter, the opposite was seen for Australian children [30]. The authors suggested that this may be a product of Australia’s winters being relatively mild compared with Canada’s, and Australia’s summers being relatively harsher.

In sum, the evidence suggests that temporal patterning in activity and diet across the year leads to cyclical spikes in weight gain, which accrue over time. However, research to date has been piecemeal, focussed on only diet, or activity patterns or weight gain, and not all three simultaneously. Additionally, Australian data are lacking; it is possible that international findings may not reflect Australian patterns, due to key differences in timing of festivities by season (e.g. Australian Christmas falls in summer) and climate (e.g. Australian winters are relatively mild and summers relatively harsh). Finally, most research on the effects of daily physical activity, sedentary behaviour and sleep has examined the activities in isolation and applied standard multivariate statistical techniques which assume that daily activities are independent. However, activity data are naturally co-dependent – they occur in a finite 24-h window, thus if one activity increases (e.g. moderate to vigorous physical activity), then another must decrease (e.g. sleep). Research employing frequent waves of data collection, taking into account the compositional nature of activity data, is required to understand temporal patterns of weight gain, activity and dietary intake in order to enable the design and implementation of interventions at the time they are needed most. For example, if most annual weight gain occurs at Christmas, and this coincides with unhealthy eating patterns, dietary interventions could be targeted in the lead up to Christmas. This aims of this study are therefore to:
Describe the annual rhythms in adults’ body weight, daily activities and eating patterns, and determine whether changes in body weight across the year are associated with changes in activity and diet compositions.Determine whether changes in children’s body mass, activity and diet compositions are related to those of their parents, andExamine whether parental factors (parenting style and home environment) are associated with changes in children’s body mass, activity and diet compositions.

## Methods

### Study design

This is a prospective cohort study “Annual Rhythms In Adults’ lifestyle and health” (ARIA) that will measure weight, daily activity, dietary intake, and wellbeing over a 12 month period. The study has been approved by the University of South Australia Human Research Ethics committee (Protocol number: 201901) and registered on the Australian New Zealand Clinical Trial Registry (Trial ID: ACTRN12619001430123). The South Australian Department for Education and Catholic Education South Australia has provided approval to match ARIA data with data from children in a concurrent cohort study, the “Life on Holidays” study [31], as further described below.

### Participants and procedure

A community-based sample of 375 predominantly middle-aged adults will be recruited from the greater metropolitan area of Adelaide, South Australia, using two methods. Firstly, all parents and guardians of children enrolled in a separate three-year cohort study, “Life on Holidays” [31], will be invited to participate via email or postal invitation. In the Life on Holidays study, 380 children were recruited from Adelaide metropolitan schools in two waves commencing Feb 2019 and Feb 2020. Schools were randomly selected and invited from low, middle and high socio-educational advantage tertiles to ensure a representative sample. Anticipating the uptake from these parents to be a challenge, given the burden of participating in simultaneous 12-month trials, a second recruitment method is planned in case it is needed. Parents meeting the inclusion criteria will also be recruited through general advertising (social media posts, paid Facebook advertisements, print media). Mirroring the Life on Holidays protocol, participants will be enrolled in two waves (December 2019 and December 2020). Inclusion criteria are parent/guardian of a child enrolled in Life on Holidays or parent/guardian of child aged 5 to 12 years, 18 to 65 years old, residing in greater metropolitan Adelaide, with access to a Bluetooth-enabled mobile device or computer and home internet, proficiency in English, and ambulant. Exclusion criteria are pregnancy, having an implanted electronic medical device, or experiencing or receiving treatment for any life-threatening condition which impacts daily lifestyle and health.

Participants will comprise two cohorts: those beginning in December 2019 and those beginning in December 2020. A baseline face-to-face home visit will be conducted between August and November in the year of commencement, where participants will have their height measured and be given a Fitbit Charge 3 activity monitor and Fitbit Aria body weight scale (Aria 2 or Aria Air scale; Fitbit Inc., San Francisco, CA, USA). Participants will be asked to wear the activity monitor continuously except during water-based activities, and to weigh themselves daily. To enable remote collection of daily activity and weight data, participants will authorise bespoke software, “Fitnesslink”, to access their Fitbit user account data, including user profile details, sleep, activity and weight data, and device data (battery status and time of most recent sync).

Participants will complete a baseline survey about their demographic, health, and lifestyle characteristics either before or during the home visit. They will also complete eight online surveys about recreational physical activity, dietary intake, psychological wellbeing, weight perception/management, and work/holiday status over 12 months (see Fig. 1). Four of the online surveys are scheduled to coincide with assessments conducted in the Life on Holidays study to allow for within-family comparisons.

**Fig. 1 Fig1:**
[figure not shown]
ARIA assessment schedule. Bars indicate continuous assessment. Full dots indicate assessments coinciding with Life on Holidays assessments. Empty dots indicate assessments at additional timepoints

Upon completion of the study, participants will be provided an honorarium of $100 and will be allowed to keep the Fitbit Charge 3 and weight scales.

### Measures

#### Body weight

Body weight will be measured using Fitbit Aria electronic weight scales (Fitbit Inc., San Francisco, CA, USA) [32, 33]. Participants will be encouraged to weigh themselves preferably daily but at least weekly, in the morning, whilst wearing minimal clothing, prior to meals and after voiding. Participants who do not wish to weigh in the morning will be asked to weigh at the same time on each occasion. Body weight data will be uploaded to participants’ Fitbit accounts and collected remotely via the Fitnesslink software. Height will be measured at baseline home visit using a stadiometer (Leicester Height Measure MKII). Measures will be conducted according to International Society for the Advancement of Kinanthropometry assessment procedures [34].

#### Daily activity composition

Daily activity composition will be measured continuously using Fitbit Charge 3 activity monitors (Fitbit Inc., San Francisco, CA, USA). Participants will be asked to wear the device on their non-dominant wrist 24-h a day, except during water activities and device charging, and to sync data to their Fitbit account at least every 5 days. Data will be collected remotely via the Fitnesslink software, created especially for this study. Each minute in every 24-h period will be classified as sleep, sedentary, light, moderate or vigorous physical activity according to Fitbit’s proprietary algorithm, which also provides bedtime and rise time. Minutes classified as sedentary (recorded when no other activities are detected) AND with missing heart rate data will be classified as non-wear. Fitbit activity monitors are commonly used in biomedical research [35, 36] and have acceptable validity for moderate-to-vigorous physical activity (Fitbit Flex compared to Actigraph GT3X+ *r =* 0.731 [37]), sleep (Fitbit Charge 2 compared to polysomnography sensitivity = 0.96, specificity = 0.61 [38]; Fitbit Flex compared to polysomnography *r =* 0.97 [39]) and total daily energy expenditure (Fitbit Flex compared to doubly labelled water in free-living conditions r_s_ = 0.84 [40]).

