#### Recreational activity.

Recreational physical activity will be assessed at each timepoint using items from the How Areas in Brisbane Influence Health and Activity (HABITAT) study [41] which will be modified to reflect recreational activity over the previous month. Participants rate how often they did 15 activities (e.g. running or jogging, team sports, water activities) on a 5-point scale (never, once a month, once every 2 weeks, once a week, more than once a week). Participants will also report the number of hours they watch television or use an electronic device (computer, tablet, smartphone, video games) in their free time (1) on typical a weekday and (2) on typical a weekend day.

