### Statistical analysis

Longitudinal compositional data analysis methods will be used to assess activity and diet compositions. To account for the inherent co-dependency of compositional parts (proportions of time or macronutrients), compositions will be expressed as sets of isometric log ratios (ilrs) before their inclusion in statistical models [63, 64]. Aim 1 will use data from all participants. Aims 2 and 3 will use data only from parents/guardian of children enrolled in Life on Holidays and matched data from children in Life on Holidays.

#### Aim 1

Annual rhythms will be described graphically using Loess curves. Associations between change in weight (dependent variable) and changes in activity and diet compositions (independent variables) will be examined using multilevel modelling to adjust for non-independence of data, allowing for nesting of repeated measures within individuals and individuals within families. Diet and activity will be examined simultaneously to identify unique effects on weight. Covariates will include age, sex, socioeconomic status, and total energy intake.

#### Aim 2

Associations between change in children’s (dependant variables) and parents’ (independent variables) weight, activity, and diet compositions will be examined using a series of multilevel models to adjust for non-independence of data. Covariates will include parental and child age, sex, socioeconomic status, and child total energy intake.

#### Aim 3

Factor analysis will be used to derive factors from the baseline family environment items. The association between change in children’s body mass index z-score, and activity and diet compositions (dependant variables) and family environment (independent variable) will be examined using a series of multilevel models. Covariates will include parental and child age, sex, socioeconomic status, and total energy intake.

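### Water-based exercise is never recorded because the tracker is taken off for it, so MVPA is understated in people who do it and the annual activity rhythm may be distorted

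*Protocol article*

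**What the plan says.** The instruction to remove the tracker appears twice in the Methods of the protocol article. Under Participants and procedure, participants are to "wear the activity monitor continuously except during water-based activities". Under Daily activity composition, wear is "24-h a day, except during water activities and device charging".

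The same section makes the device the source of the activity data: "Each minute in every 24-h period will be classified as sleep, sedentary, light, moderate or vigorous physical activity according to Fitbit’s proprietary algorithm". It defines non-wear as follows: "Minutes classified as sedentary (recorded when no other activities are detected) AND with missing heart rate data will be classified as non-wear".

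Under Recreational activity there is a second, self-reported source: "Participants rate how often they did 15 activities (e.g. running or jogging, team sports, water activities) on a 5-point scale". The scale runs from never to more than once a week, refers to the previous month, and is asked at each timepoint. The article mentions no question on the duration or intensity of these activities.

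For Aim 1, the Statistical analysis section says "Annual rhythms will be described graphically using Loess curves". It then relates change in weight to changes in the activity and diet compositions, expressed as isometric log ratios, in multilevel models. The survey item on water activities is given no part in this. The limitations in the Discussion cover the restriction to parents, motivated volunteers, the single city and reactivity to weighing. They do not mention exercise done without the tracker.

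**The concern.** Most reasons for taking a tracker off, such as charging, have no fixed link to what the wearer is doing. Removal for water activities does have such a link, because by instruction the gap falls on an activity, and that activity is often exercise. The measured composition then has too little MVPA relative to sleep, sedentary and light time.

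Two Aim 1 results are exposed. The first is the annual activity rhythm. If water activity is commoner in the Australian summer, measured summer MVPA is pushed down. The Background cites a study of children whose result points in the same direction: "while Canadian children were relatively more active in summer than winter, the opposite was seen for Australian children". The second is the weight model, which works on change. A participant who takes up swimming for part of the year shows no rise in MVPA, or a fall if swimming replaces exercise on land.

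**Working it through.** The article gives no figure for water-activity time, expected MVPA or non-wear, so there is no stated figure to reproduce. The removal instruction, the classification rule and the survey item come from the article. Every minute value below is an assumption. Every water minute is counted as MVPA, which leans towards a larger loss.

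**1. Trace one minute of swimming.** The tracker is off, so it detects no activity and the minute defaults to sedentary. Heart rate is missing, so the minute becomes non-wear. It was never MVPA in the record, so the rule removes no MVPA. Without the rule the minute would stay sedentary. With 600 true sedentary minutes and 5 swimming minutes, the record would show 605 sedentary minutes instead of 600, which is worse.

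**2. One day.** Suppose that non-wear is dropped and the rest of the day is rescaled to 1440 minutes. The article does not say this is done. Take 60 min of MVPA on land.
- Swim of 30 min plus 15 min extra off the wrist: 60 × 1440/(1440 − 45) = 61.9 min, against a true 90 (−31%).
- Swim of 60 min plus 20 min extra: 60 × 1440/(1440 − 80) = 63.5 min, against a true 120 (−47%).

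Rescaling recovers almost nothing, because the lost minutes are a large share of MVPA and a tiny share of the day.

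**3. Cohort mean in a season.** Loss per day = proportion doing water activity × weekly minutes / 7. Assume a proportion of 0.1 to 0.3, 60 to 180 min a week, and MVPA on land of 30 to 60 min/day.
- Low end: 0.1 × 60/7 = 0.9 min/day; 0.9/(60 + 0.9) is about 1% of true mean MVPA.
- High end: 0.3 × 180/7 = 7.7 min/day; 7.7/(30 + 7.7) is about 20%.

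**4. Summer against winter, with true MVPA the same in both.** Recorded MVPA = (T − w) × 1440/(1440 − w), where T is true MVPA including water exercise and w is water minutes per day.

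| T (min/day) | w, summer vs winter | Recorded summer | Recorded winter | False difference |
|---|---|---|---|---|
| 40 | 2 vs 0.5 | 38.1 | 39.5 | −3.7% |
| 40 | 5 vs 1 | 35.1 | 39.0 | −10.0% |
| 40 | 10 vs 2 | 30.2 | 38.1 | −20.6% |
| 30 | 5 vs 1 | 25.1 | 29.0 | −13.6% |
| 60 | 5 vs 1 | 55.2 | 59.0 | −6.5% |
| 40 | 5 vs 5 | 35.1 | 35.1 | 0 |

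The row with 10 min/day exceeds the largest cohort average in step 3 (7.7 min/day), so it is better read as one regular user than as the cohort. Larger inputs give larger dips (28.2% at T = 30 with 10 vs 2), but they too need water time above that average. With equal water time the level is too low and the seasonal contrast is unaffected.

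**5. On the log-ratio scale.** The ratio of MVPA to the other parts is the same whether or not the day is rescaled. For T = 40 and 5 vs 1, the shift in the MVPA log ratio is √(3/4) × ln(35/39) = −0.09. The transformation therefore does not repair the loss.

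**The case against.** Several objections have force.

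- **The non-wear rule is not at fault.** A reader might infer that it deletes exercise. It does not: the loss comes from removing the device, and the rule keeps the gap from being counted as sedentary time. This stands in full.
- **Seasonality is not documented.** Nothing in the article says that water activity clusters in summer. The cited seasonal pattern concerns children, and its authors put it down to climate. A reader might go further and expect the sign of the summer-winter difference to reverse, or the children's pattern to be falsely confirmed in adults. A reversal is easily constructed: if 20% of participants swim 90 min a week in summer and 15 in winter, the differential loss is 0.2 × (90 − 15)/7 = 2.1 min/day. With MVPA on land 1 min/day higher in winter, a true contrast of about +1.1 becomes −1.0. But this follows from the inputs chosen. Any true contrast between 0 and 2.1 would flip, and a larger one would not. The documents support neither inference.
- **Not all water time is exercise.** The term is undefined and could include wading or supervising children. This stands, and it makes the figures above lean high.
- **Non-wear handling and sensitivity analyses are commonly left to an analysis plan.** This is so, and their absence from an article is not the point here. The point rests on two things the article fixes: the tracker comes off for water activities, and the device alone supplies MVPA. A later plan could add a check, but it could not recover the minutes from an item that records frequency only.

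**Conclusion.** The concern holds as a bias built into the measurement. MVPA is understated for participants who do water activities at that intensity, and nothing in the article corrects or acknowledges it. Bias in the annual rhythm and in the within-person activity-weight association depends on water activity varying over the year, which is plausible but not documented. If it is commoner in summer, summer activity will look too low.

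The size cannot be computed from the documents. Under the assumptions shown it runs from negligible (about 1%) to about 20% of mean MVPA, and it is zero for the seasonal contrast if water time is equal across seasons. It does not invalidate Aim 1. It does mean that a modest seasonal difference in MVPA cannot be taken at face value without a check, and the data for that check are already being collected.

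**What to change.** In the Statistical analysis section, under Aim 1:

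1. Report non-wear minutes by month.
2. Repeat the activity rhythm and the weight model as sensitivity analyses by reported frequency of water activities, including an analysis limited to participants who report none at every survey.
3. State in advance that a seasonal MVPA difference that is absent in that group will be treated as possibly due to device removal.

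In the Discussion, add the loss of water-based exercise to the limitations.

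This costs some added analysis and a sentence or two, with no new device, visit or question. The group reporting no water activity is smaller and is selected on an activity behaviour, so its curve is a check and not a replacement. Its definition is also incomplete: eight surveys that each recall one month cover at most eight of the twelve months.

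A question on minutes per session could be added to the survey, with reported minutes added back to MVPA. This is optional and should not replace the device-based curve. It would cover only the survey months, which could put steps into a curve built from continuous data, and it would need an assumed intensity.
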